**Methods:**

A pilot and national trial will measure implementation feasibility, acceptability, and effects of the MPACT intervention on treatment practice change, clinic culture, patient retention, and patient posttraumatic stress symptoms (PTSS). The pilot will be a single-arm 5.5-month pilot study of MPACT conducted in 2 Arizona methadone treatment clinics (rural and urban) among 100 patients and 22 staff. The national trial will be a 20-month cluster randomized trial conducted among 30 clinics, 600 patients (20 per clinic), and 480 staff (18 per clinic). Data will be gathered by staff and patient surveys and patient chart review. The primary study outcome is increased patient methadone treatment retention measured as (1) time to first treatment interruption from study enrollment; (2) active in treatment at enrollment, day 30, 60, 90, and 120; and (3) continuous days in treatment during the study period. Secondary study outcomes include reductions in vicarious trauma and PTSS among enrolled opioid treatment program staff and PTSS among enrolled patients.

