#### Accredited Psychoeducational Training

A jointly accredited, self-paced, 3-module psychoeducational training focused on (1) the definition and application of low-barrier, patient-centered, trauma-informed methadone treatment; (2) public and clinic policy (federal and state); and (3) clinic staff opportunities to increase patient-centered, trauma-informed methadone treatment. The training seeks to empower staff to initiate any positive change at the individual and staff group levels. Joint accreditation offers continuing medical education for physicians and nurses as well as continuing education credits for social workers, psychologists, peer support specialists, case managers, and administrators. Training completion is incentivized by the award of 3 free continuing education credits according to professional discipline. While training is voluntary, to receive the continuing education credits, staff of MPACT-enrolled clinics must complete the training within 2 weeks of the MPACT launch within the clinic. New staff can complete the training as they are hired during the MPACT intervention period. This modular training approach was adapted from a prior successful project focused on increasing pharmacy syringe sales to people who use drugs [34].

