### Study Recruitment

Recruitment is stepwise for both the pilot and the trial. For the national trial, clinics will first be recruited through email from a national list of methadone clinics responding to a prior survey by this team during 2024 [60]. A second strategy will involve an email to the state opioid treatment authority with a request to forward study information and the recruitment flyer to methadone clinic directors in their state. State opioid treatment authorities are the single opioid regulator in each state. Clinics that allow study recruitment among staff and patients, establish a DSA for the transfer of patient participant methadone treatment chart data at the conclusion of the 20-month trial, and identify a clinic “champion” to assist with study enrollment and study contact will be eligible for randomization as described below.

Following clinic enrollment, each clinic champion will post recruitment flyers in staff-only areas (for staff participants) and in patient-only areas (for patient participants). Recruitment flyers for staff lead to a study portal (web-based) presenting information about the study and requesting agreement to participate. If agreement is made, staff participants will immediately complete the enrollment survey (baseline assessment 1). The same process will occur for patients. Payment for timely completion of each survey is US $20 for patients and staff. This cost was determined by a group of staff and patients who completed the work associated with aim 1.

Patient and staff confidentiality will be maintained by centralizing the enrollment process. Recruitment flyers will be displayed in staff-only and patient-only areas with a QR code or URL leading to information for potential participants to learn more about the study and to voluntarily enroll. This process ensures the anonymity of study participants within the clinic, meaning that patients and staff participants will not be known to the study clinic. Further, at the time of enrollment, a unique identifier will be established by the participant and will be used henceforth. At no time will the clinic leadership or clinic champion know the identity of the study participants. The only exception to this is at the conclusion of the study when patient chart data transfer will occur, and at that time, only 1 person handling data transfer will have the name and dates of birth of the participants whose charts will be transferred for study purposes.

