### Phase 2, Years 3-6: Hybrid, Cluster Randomized Controlled Trial

#### Overview

Aim 4: Quantify the effects of MPACT on methadone treatment practice change and clinic culture.Aim 5: Determine the efficacy of MPACT on methadone treatment retention and patient and staff PTSS outcomes.Aim 6: Evaluate the effect of patient and staff trauma on primary outcomes and staff MPACT implementation.

Findings from the pilot study will determine the preliminary effect size to confirm power analyses and final sampling for a hybrid type 1, 20-month cluster randomized controlled trial among 30 clinics, 600 patients (20 per clinic), and 480 staff (18 per clinic). This hybrid type 1 trial will focus primarily on MPACT’s effect outcomes while examining the association of MPACT implementation fidelity and acceptability and identifying the multilevel factors influencing implementation.

For the trial, the clinic is the unit of randomization. The intervention condition will be the MPACT intervention, and the control condition will involve accredited training about methadone that does not overlap aspects of the MPACT intervention. As shown in Table 2, we will allow a 20-month study period to accommodate staggered trial initiation through month 12 of year 2. Given the 20-month trial period, we will allow for new staff members to enroll through the end of the 7th month of their site’s trial period.

**Table 2 table2:** Cluster randomized controlled trial of Methadone Patient Access to Collaborative Treatment.

	Year 1			Year 2			Year 3			Year 4	
	Half 1	Half 2	Half 1		Half 2	Half 1		Half 2	Half 1		Half 2
Intervention arm clinics (n=15)	Start-up	Intervention	Intervention		Intervention	Intervention		Intervention	Intervention		Closeout
Control arm clinics (n=15)	Start-up	Usual care	Usual care		Usual care	Usual care		Usual care	Usual care		Closeout
Key processes	Randomization process finalized	Trial allows for staggered starts based on recruitment	Trial allows for staggered starts based on recruitment		Trial allows for staggered starts based on recruitment	Trial follow-up		Trial follow-up	Trial follow-up		Trial outcome analyses and dissemination

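### The staff sample size for the cluster randomized trial contradicts itself: 30 clinics at 18 staff each is 540, not 480

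*Protocol article*

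**What the plan says.** The Methods paragraph of the abstract describes a trial "conducted among 30 clinics, 600 patients (20 per clinic), and 480 staff (18 per clinic". The Overview under Phase 2 repeats the same figures: "30 clinics, 600 patients (20 per clinic), and 480 staff (18 per clinic". Table 2 confirms the number of clinics by arm: "Intervention arm clinics (n=15" and "Control arm clinics (n=15", which makes 30.

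Three other statements bear on who counts as staff:

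- The Phase 2 Overview sets the entry window: "we will allow for new staff members to enroll through the end of the 7th month of their site’s trial period".
- Study Recruitment says that, once they agree, "staff participants will immediately complete the enrollment survey (baseline assessment 1".
- Accredited Psychoeducational Training says of the MPACT clinics: "New staff can complete the training as they are hired during the MPACT intervention period".

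The Measures section lists staff vicarious trauma and staff posttraumatic stress symptoms as secondary outcomes. The Phase 2 Overview also says that the pilot will be used to confirm the power analyses and the final sampling.

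**The concern.** A total, a number of clusters and a number per cluster are tied together by one multiplication, and here all three are stated. For patients they agree. For staff they do not, so at least one of the staff figures is wrong as written. Because the mismatch occurs identically in two places, it does not look like a slip confined to one sentence.

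What is at stake is the staff recruitment target, overall and per clinic, and the planned precision of the staff outcomes. The article gives no power calculation for staff, so nothing else in it shows which figure was intended. The per-clinic number also matters for implementation reporting, because reach is measured partly by the number and proportion of staff taking part at each clinic.

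The entry window adds an ambiguity: the article does not say whether the stated total includes staff who join after their site has started.

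**Working it through.** **Inputs.** 30 clinics, 600 patients, 20 patients per clinic, 480 staff and 18 staff per clinic (abstract; Phase 2 Overview); 15 clinics per arm (Table 2). The intraclass correlations of 0.05 and 0.10 are those named for patients in Statistical Analysis. Applying them to staff is an assumption, since the article gives none for staff.

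**1. Total = clinics × number per clinic.**
- Patients: 30 × 20 = 600. The stated figure is reproduced.
- Staff: 30 × 18 = 540. The stated 480 is not reproduced.
- Gap: 540 − 480 = 60, or 30 per arm. That is 60/480 = 12.5% of the lower figure and 60/540 = 11.1% of the higher.

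**2. Can the stated figures be reconciled?**
- Keep 480 and 30 clinics: 480/30 = 16 per clinic, not 18.
- Keep 480 and 18 per clinic: 480/18 = 26.7 clinics, which is not a whole number and not 30.
- Treat 480 as evaluable and 540 as recruited: 480/(1 − d) = 540 needs d = 11.1%. With d = 10%, 480/0.9 = 533.3, rounded up to 534, or 17.8 per clinic, which rounds to 18. The arithmetic is possible, but the article states no staff attrition rate and does not label either number this way.

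**3. What the gap does to precision (illustration).** With m staff per clinic and equal clinic sizes, the design effect is 1 + (m − 1) × ICC and the effective N is 30m divided by it. The detectable standardized difference at 80% power and two-sided 5% is (1.960 + 0.842) × √(4 / effective N), with no baseline adjustment.

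| ICC | Staff per clinic | Total | Design effect | Effective N | Detectable difference (SD) |
|---|---|---|---|---|---|
| 0.05 | 16 | 480 | 1.75 | 274 | 0.34 |
| 0.05 | 18 | 540 | 1.85 | 292 | 0.33 |
| 0.10 | 16 | 480 | 2.50 | 192 | 0.40 |
| 0.10 | 18 | 540 | 2.70 | 200 | 0.40 |

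**4. The entry window.** At 30.44 days per month, the end of month 7 is about day 213 and month 20 is about day 609. That leaves about 396 days, and 396/77 = 5.1, so the last permitted entrant has room for 5 of the 7 follow-up surveys before the site's 20 months end. Whether such a person counts as one of the 480 (or 540) is not stated.

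**The case against.** The strongest reply is that the slip changes almost nothing. Statistical Analysis sizes the trial on patient treatment interruption alone, with 30 clinics of 20 patients, and those figures agree. No staff power statement rests on 480 or 540, and the table above shows nearly the same detectable difference either way. The sample is also described as provisional until the pilot is analyzed. All of this stands as to consequence. It does not remove the error: provisional status explains why a number may change later, not why one sentence holds two incompatible numbers.

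A reader might infer more from the entry window: that staff membership is open-ended, that late joiners in MPACT clinics give a baseline already affected by the intervention in one arm only, and that pooling them biases the staff comparison. The article does not support this. The window is explicit and closes at month 7. The baseline survey is completed on agreeing to take part, and nothing says that training comes first; a new hire could enroll before any training. Exposure before baseline is possible for some late entrants, but its extent is unknown. The article states no staff model, pooling rule or staff analysis set, and these commonly sit in a statistical analysis plan, which is not shown here.

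Nor is there a good case for requiring that later entrants be left out of the main staff analysis. MPACT deliberately includes newly hired staff, so leaving them out would change the population being studied.

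**Conclusion.** The inconsistency is certain and rests only on figures in the article. The documents do not show which staff figure is intended. An evaluable-versus-recruited explanation would need roughly 10 to 11% attrition, which is nowhere stated.

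The effect is confined to the staff recruitment target and the secondary staff outcomes. Under the assumed intraclass correlations, the standard error would be about 3% larger with 480 than with 540 at 0.05 (√(292/274) = 1.03) and about 2% larger at 0.10 (√(200/192) = 1.02). The primary patient outcome and its power statement are unaffected. Late staff entry is a stated design feature; a baseline that may in some cases follow exposure, and a shortened follow-up, are points for the analysis plan to handle.

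**What to change.** Give one matching pair in both the abstract and the Phase 2 Overview: either 480 staff at 16 per clinic, or 540 staff at 18 per clinic. In the Overview, add a clause saying whether the total is recruited or evaluable (with the attrition assumption if the two differ) and whether staff enrolling up to month 7 count toward it.

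The cost is two corrected sentences and one added clause, with no change to the design or to the patient analysis. If 540 is the intended figure, participant payments for the additional 60 staff would be at most 60 × US $160 = US $9,600, using the trial remuneration given under Ethical Considerations.

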#### Clinic Stratification Factors

By the time of trial planning finalization, we anticipate that the state regulatory environment in each trial location will be a likely outer setting impact. Given the importance of state policy for regulating OTPs and methadone treatment, we will measure state regulatory favorability toward OTPs using a 2-level coding structure used in prior studies by this team [60]. We will code state laws based on the Pew state regulatory review [8] as “expanding methadone access” or “not expanding or limiting access.” Randomization to trial condition will be stratified based on outcomes of this state regulatory coding.

### Statistical Analysis

Our primary outcome is patient time to first treatment interruption (confirmed in the pilot). Secondary outcomes include treatment retention (yes or no) at selected time points (1, 3, 6, and 12 months) and time to treatment discontinuation. To accommodate the clustering induced by nesting patients within clinics, we will use a mixed effects Cox proportional hazards model (shared frailty model) [61,62] to accommodate differential survival probability among clusters. The mixed model will include a random intercept for the clinic and a fixed treatment effect for MPACT or control assignment. We will also include patient-level covariates for age, sex, and time in MMT.

Our initial sample size calculation uses asymptotic normal results for log hazard ratio as well as sample size inflation factors (eg, Donner) [62] for cluster randomized trials. In designing the future R33 trial, we will make use of specific sample size methods for cluster randomized trials with time-to-event outcomes [63,64]. The relative frequency of first treatment interruption [65] is estimated as 66% at 12 months of MMT until we have confirmation from the pilot. We evaluate the number of clinics and number of patients, assuming that MPACT intervention reduces this frequency to 45% (n=240), 50% (n=300), and 55% (n=330). The power curves based on independent observations (no cluster effect) are shown in Figure 3. The graph shows that the recruitment of 30 clinics, with 20 patients per clinic, provides greater than 80% power to detect a difference in treatment interruption rates of 66% (control) and 55% (MPACT) with α=.05. Consistent with the cluster randomization trial design, we also consider the average number of patients per clinic as 10, 20, and 40 and different degrees of intraclinic clustering using intraclass correlation coefficients of 0.05 and 0.10.

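### Clinic randomisation is stratified by state regulation, but the stated primary frailty model omits the stratum; if the stratum is prognostic, the test is conservative and power is lost

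*Protocol article*

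**What the plan says.** Two sections of the protocol article bear on this.

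**Clinic Stratification Factors.** The authors give a reason for expecting state policy to matter: "we anticipate that the state regulatory environment in each trial location will be a likely outer setting impact". They set out how it will be captured: "we will measure state regulatory favorability toward OTPs using a 2-level coding structure used in prior studies by this team". They then use it in the design: "Randomization to trial condition will be stratified based on outcomes of this state regulatory coding". The Phase 2 Overview fixes the level at which this happens: "For the trial, the clinic is the unit of randomization".

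**Statistical Analysis.** The primary outcome, time to first treatment interruption, is to be analysed with a shared-frailty Cox model. Its terms are named in two sentences: "The mixed model will include a random intercept for the clinic and a fixed treatment effect for MPACT or control assignment", and then "We will also include patient-level covariates for age, sex, and time in MMT". The state code is listed neither as a covariate nor as a stratum of the baseline hazard. Nothing elsewhere in the article says that the analysis will account for the stratification.

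**The concern.** Each clinic sits in one state, so the stratum is a clinic-level variable. Treatment is also assigned at clinic level, so the standard error of the treatment effect is driven largely by the variance between clinics. Leaving the stratum out puts whatever it explains into the clinic frailty variance. The three named covariates are measured on patients and cannot stand in for it.

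Stratified allocation makes the treatment estimate less variable when the stratum is prognostic. A model without the stratum does not know this and reports the larger standard error. Intervals are then wider than they need be, and the test rejects less often than its nominal level allows. With 30 clinics, precision that the design has already secured should not be given up in the analysis.

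**Working it through.** **Inputs from the article (Statistical Analysis; Phase 2 Overview).** 30 clinics, 15 per arm, 20 patients each, 600 patients; interruption 66% in control and 55% under MPACT; alpha 0.05; ICC values 0.05 and 0.10; power curves drawn for independent observations.

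**Assumptions, because the article gives no figure.** Two-sided test. Share R² of between-clinic variance explained by the stratum: 0%, 10%, 25% or 50%.

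**Step 1: the plan's own figure.** The article states: "The graph shows that the recruitment of 30 clinics, with 20 patients per clinic, provides greater than 80% power". Converting the rates to a hazard ratio, HR = ln(0.45)/ln(0.34) = 0.740, so |ln HR| = 0.301. Expected events = 300 × (0.66 + 0.55) = 363. The Schoenfeld formula gives power = Φ(0.301 × √363 / 2 − 1.96) = 81.8%. The stated figure is reproduced, with no clustering. (A plain comparison of two proportions gives 78.8%.)

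**Step 2: clustering, stratum included or omitted.** With 20 patients per clinic:

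- stratum omitted: DE₀ = 1 + 19 × ICC, which is 1.95 at ICC 0.05 and 2.90 at ICC 0.10;
- stratum included: DE₁ = 20 × [ICC × (1 − R²) + (1 − ICC)/20].

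The matching standard errors are SE₀ = 2√(DE₀/363) and SE₁ = 2√(DE₁/363). Under stratified randomisation the true variability is SE₁ in both cases. The model without the stratum reports SE₀. Therefore:

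- power, stratum omitted = Φ((0.301 − 1.96 × SE₀)/SE₁);
- power, stratum included = Φ(0.301/SE₁ − 1.96);
- type I error, stratum omitted = 2Φ(−1.96 × SE₀/SE₁).

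Worked case, ICC 0.05 and R² 50%: DE₁ = 20 × (0.025 + 0.0475) = 1.45; SE₀ = 0.147; SE₁ = 0.126; ratio 1.16. Power is 54.3% omitted and 66.3% included; type I error omitted is 2.3%.

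| ICC | R² | DE₀ → DE₁ | SE₀/SE₁ | Power omitted | Power included | Gain (points) | Type I error omitted |
|---|---|---|---|---|---|---|---|
| 0.05 | 0% | 1.95 → 1.95 | 1.000 | 53.7% | 53.7% | 0 | 5.0% |
| 0.05 | 10% | 1.95 → 1.85 | 1.027 | 53.8% | 55.9% | 2.1 | 4.4% |
| 0.05 | 25% | 1.95 → 1.70 | 1.071 | 53.9% | 59.4% | 5.5 | 3.6% |
| 0.05 | 50% | 1.95 → 1.45 | 1.160 | 54.3% | 66.3% | 12.0 | 2.3% |
| 0.10 | 0% | 2.90 → 2.90 | 1.000 | 39.1% | 39.1% | 0 | 5.0% |
| 0.10 | 10% | 2.90 → 2.70 | 1.036 | 38.7% | 41.5% | 2.8 | 4.2% |
| 0.10 | 25% | 2.90 → 2.40 | 1.099 | 38.0% | 45.6% | 7.6 | 3.1% |
| 0.10 | 50% | 2.90 → 1.90 | 1.235 | 36.6% | 54.8% | 18.2 | 1.6% |

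**Step 3: simulation check.** 20,000 replicates used a regression of clinic-level log hazards with a t-test, as a proxy for the frailty Cox model. Assumed: strata of 16 and 14 clinics, residual clinic SD 0.25 on the log-hazard scale.

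| Stratum HR | Type I error omitted | Type I error included | Power omitted | Power included |
|---|---|---|---|---|
| 1.00 | 5.0% | 5.0% | 55% | 55% |
| 1.22 | 4.0% | 4.7% | 52% | 54% |
| 1.49 | 2.4% | 4.7% | 44% | 54% |
| 1.82 | 1.1% | 4.8% | 33% | 53% |

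The direction agrees with Step 2. When the stratum has no effect, including it costs almost nothing (55.2% against 55.1%).

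**The case against.** **The list of terms may be open.** The article never calls it complete. The covariate sentence concerns patient-level terms, trial planning is described as still being finalised, and an analysis plan could add the stratum. This is the strongest point, but it does not carry. The article names the model's terms down to age and sex, does not defer others, and nowhere says that the analysis will reflect the stratification. An analysis plan that followed the text faithfully would carry the mismatch forward.

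**The size is assumed.** This stands. The article expresses an expectation that state policy matters and gives no effect size. At 10% of between-clinic variance the gain is only 2 to 3 points, and at 0% it is nil. A reader might infer that the standard error is too large in any event; that follows only if the stratum is prognostic.

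**The error is conservative.** This also stands. The clinic random intercept absorbs the stratum differences, so the test does not reject too often. A reader might infer that the primary test is invalid; the calculations show type I error at or below 5%.

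**Imbalance.** A reader might also infer that chance imbalance of strata between arms goes uncorrected. The documents do not support that as a harm: stratified randomisation is there to limit such imbalance, and 15 clinics per arm are planned.

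**Low power is a separate matter.** The 54% and 39% baselines arise from applying the article's ICC values to a power statement that assumed independence. That issue exists with or without the stratum term and is not evidence for this point.

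**Conclusion.** The mismatch is real: the trial randomises within state-regulation strata, and the stated primary model ignores them. The consequence is a loss of efficiency. It is no threat to validity. Over the assumed range of 0% to 50% of between-clinic variance explained, the reported standard error is 0% to 16% too large at ICC 0.05 and 0% to about 24% too large at ICC 0.10. The power forgone is 0 to 12 points and 0 to 18 points respectively. The upper ends require a strongly prognostic stratum, which the documents neither claim nor exclude. The figures also rest on a two-sided 5% test, equal clinic sizes of 20, and a design-effect approximation to the frailty model. The change is worth making because its cost is negligible in every scenario, while its benefit ranges from nothing to substantial.

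**What to change.** State in the protocol or the analysis plan, before outcome data are seen, that the primary shared-frailty Cox model has fixed effects for treatment and for the two-level state regulatory stratum, a random intercept for clinic, and the named patient-level covariates. Use the same stratum term in the models for the secondary retention outcomes (retention at the selected time points and time to discontinuation).

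The cost is one line of text and about one clinic-level degree of freedom (28 to 27 with 30 clinics). No extra data are needed. State laws have still to be coded, but the code must exist for every clinic before that clinic can be randomised within its stratum.

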### Measures

The primary study outcome is increased patient methadone treatment retention. This outcome is measured in three ways: (1) time to first treatment interruption, calculated as the number of days to first missed dose from day 0 (MPACT enrollment); (2) evidence of being active in treatment, a binary (yes or no) if receiving dose at points in time on day 0, 30, 60, 90, and 120; and (3) continuous days in treatment during the study period, calculated as time (days) to discharge. Data measuring this outcome are gathered by patient surveys and chart reviews.

Secondary study outcomes include reductions in VT and PTSS among enrolled clinic staff and PTSS among enrolled patients. Data measuring secondary outcomes are gathered by a survey of staff and patients enrolled in the study. For staff and patients, PTSS are measured using the 8-item posttraumatic stress disorder symptoms screener otherwise known as the PCL-5 [35]. Staff VT is measured by the Vicarious Trauma Scale [37], burnout is measured by a 3-item scale [45], and compassion satisfaction and compassion fatigue are measured by the shortened, 9-item Professional Quality of Life Scale for staff [46].

The degree to which methadone treatment is patient-centered is also a secondary outcome measured through staff surveys (assessing whether they believe they are providing it) and patient surveys (assessing whether they feel they are experiencing it). Patient-centered care competency is measured by a 19-item scale [47] including the following subscales: respecting patient perspectives, promoting patient involvement in the care process, providing patient support, and advocating for patients. Patient-centered care, as defined by the study team, is measured using a 5-item instrument that reflects the concepts of patient-centered care introduced during the accredited training modules. This scale is administered to staff, with an adapted version used for patients.

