Other individual-level variables of interest for the staff participants include (1) personal characteristics—demographics, personal substance use disorder and treatment experience, and trauma exposure history (measured by the Life Events Checklist-5) [48]; (2) work characteristics—training, education, and licensure related to their clinic role; (3) empowerment using a 5-item empowerment scale [49]; (4) stigma—toward people with OUD with a 9-item scale [50], self-stigma with a 9-item scale [51], and fear of enacted stigma through a 9-item scale [52]; (5) beliefs—about trauma-informed care measured by the attitudes toward trauma-informed care [53] and about abstinence measured by the Abstinence Orientation Scale [54]; (6) comfort with targeted practices related to the most recent federal changes to methadone treatment delivery measured by items adapted from prior studies measuring comfort with practices [34,55,56]; and (7) fidelity to MPACT—the degree to which the clinic implements the MPACT intervention.

Other individual-level variables of interest for the patient participants include (1) personal characteristics—demographics, housing, trauma history (Life Events Checklist-5), and trauma symptoms (PCL-5); (2) methadone treatment—time in treatment and dose sufficiency; (3) empowerment—as measured by a 15-item scale [57] and through an adapted 16-item Kim Alliance Scale [58]; and (4) fidelity to MPACT—the degree to which the clinic implements the MPACT intervention.

As this is a hybrid (implementation and effectiveness) pilot and trial, we are specifically focused on reach, implementation, adoption, and (in the trial) maintenance using the RE-AIM (Reach, Effectiveness, Adoption, Implementation, and Maintenance) framework [59]. Measures collected for the pilot will also be collected for the trial.

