**Methadone treatment**											
	Time in MMT^c^ and clinic, reasons for choosing methadone as treatment	—	13	—		—		—		—	
	Methadone interruption	—	2	✓		✓		✓		✓	
	Dose, sufficiency, OD^d^	—	13	✓		✓		✓		✓	

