**Implementation**											
	MPACT feasibility, accept and fit; likelihood of continuing practices	5	—	—		—		—		✓	

^a^Not applicable.

^b^SUD: substance use disorder.

^c^MMT: methadone maintenance treatment.

^d^OD: opioid overdose.

^e^LEC: Life Events Checklist.

^f^PCL-5: Posttraumatic Stress Disorder Checklist.

^g^Patients only.

^h^ProQoL: Professional Quality of Life Scale.

^i^ARTIC: attitudes toward trauma-informed care.

^j^PCQ-S: Patient-Centered Climate Scale for staff.

^k^OUD: opioid use disorder.

^l^PCC: person-centered competence.

For the 20-month trial, there will be 8 surveys from baseline assessment at enrollment through the remaining 7 assessments conducted every 77 days. Survey responses will be collected using the Qualtrics platform, accessible directly by participants.

For all enrolled patients, a review of their methadone clinic medical chart will include the duration of their treatment at the clinic, from treatment initiation to discharge or study end, whichever occurs first. This review will take place at the conclusion of the study period in accordance with the data sharing agreement (DSA) established between the clinic organization and the University of Arizona. A feasibility test with a sample of 50 charts with deidentified data was conducted in June 2024 and confirmed timely data transfer, data completeness, and utility for outcome measurement for the pilot clinics. Our national survey of OTP clinic directors found that 22.2% of clinics allowed DSAs with researchers, but the vast majority (77.3%) indicated that such agreements were not allowed or that they were not aware of the clinic organization’s position on them [60]. For the purposes of the trial, then, only clinics allowing DSAs will be eligible for study enrollment. The following medical chart segments will be requested for each patient participant: (1) the digest of the patient history of starting and leaving treatment at that clinic (dates), (2) case notes, (3) discharge summary, (4) treatment plans, (5) milligram dosing, and (6) take-home medication status over time. Case notes include qualitative data on patient stability, challenges reported by the patient (eg, housing, transportation, safety, and dosing sufficiency), and instances of missed doses. For the trial, the data will be transferred using unique identifiers that will correspond with the study unique identifiers. No personally identifying information (name and street address) will be transferred.

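### The primary Cox model omits prior treatment interruption although the trial already collects it; the analysis stays valid but gives up some power

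*Protocol article*

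**What the plan says.** The Statistical Analysis section makes patient time to first treatment interruption the primary outcome. The Measures section defines it as days from enrolment to the first missed dose. The model is a shared-frailty Cox model: "The mixed model will include a random intercept for the clinic and a fixed treatment effect for MPACT or control assignment". The next sentence reads: "We will also include patient-level covariates for age, sex, and time in MMT".

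Three other places show that the history of the same outcome is collected:

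- Table 1 gives patients two items on "Methadone interruption" at assessment 1 and repeats them at assessments 2 to 5.
- The Measures section says "Measures collected for the pilot will also be collected for the trial".
- The Data Collection section, after Table 1, has the chart review run "from treatment initiation to discharge or study end, whichever occurs first". The requested chart segments include start and leave dates at that clinic, milligram dosing, and case notes that record missed doses.

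Randomisation is by clinic, 15 per arm in Table 2, and is stratified only on state regulatory coding (Clinic Stratification Factors).

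**The concern.** A patient's earlier missed doses are a plausible predictor of the next one. Time in MMT measures how long someone has been treated, not how regularly they have dosed, so it is at best a partial proxy. Neither the stratification nor the model uses the interruption history.

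Omitting a prognostic covariate from a Cox model pulls the estimated treatment effect toward the null and costs power. Power is what is at stake here. The stated figure of more than 80% is for independent observations, and the article's own ICCs take it well below that.

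**Working it through.** **Inputs from the article.** Interruption 66% (control) versus 55% (MPACT); 30 clinics × 20 patients = 600; α = 0.05, taken as two-sided because the side is not stated; ICC 0.05 and 0.10.

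**Reproducing the stated power.** HR = ln(0.45)/ln(0.34) = 0.740, so |ln HR| = 0.301. Events = 300 × (0.66 + 0.55) = 363. Power = Φ(|ln HR| × √events / 2 − 1.96) = Φ(2.866 − 1.96) = 81.8%. This matches the stated figure, with no clustering.

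**With the article's ICCs.** The design effect is 1 + 19 × ICC.

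- ICC 0.05: 363/1.95 = 186.2 effective events; power = Φ(2.053 − 1.96) = 53.7%.
- ICC 0.10: 363/2.90 = 125.2 effective events; power = Φ(1.683 − 1.96) = 39.1%.

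**Effect of the covariate (assumed strengths).** The simulation used 30 × 20 patients, follow-up to 12 months, a true treatment log HR of −0.301, a clinic log-hazard SD of 0.25 and a binary prior-interruption covariate of about 50% prevalence. Prevalence varied between clinics. Each data set was analysed with and without the covariate, using a Cox model with clinic-robust standard errors and t on 28 df.

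| Covariate HR | Clinic SD of logit prevalence | Runs | Power without | Power with | Gain (points) |
|---|---|---|---|---|---|
| 1.5 | 0.3 | 300 | 54.7% | 55.0% | 0.3 |
| 1.5 | 0.6 | 300 | 55.7% | 58.0% | 2.3 |
| 1.5 | 0.6 | 400 | 55.5% | 55.7% | 0.2 |
| 2 | 0.3 | 300 | 55.0% | 58.7% | 3.7 |
| 2 | 0.6 | 400 | 52.7% | 58.0% | 5.3 |
| 3 | 0.3 | 400 | 50.0% | 58.5% | 8.5 |
| 3 | 0.6 | 400 | 51.5% | 61.3% | 9.8 |

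The Monte Carlo error of each power is about 2.5 to 2.9 points. Both models were fitted to the same data, so the gains are better determined than the powers. The clinic SD was set directly and not calibrated to an ICC of 0.05, but the unadjusted power of 50% to 56% is close to the 53.7% above. Age, sex and time in MMT were not simulated, so the covariate HR should be read as its effect over and above them.

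Most of the gain comes from removing attenuation. At a covariate HR of 3, the mean treatment log HR moved from −0.277 to −0.309 in one scenario and from −0.268 to −0.296 in the other. Its SD hardly changed (0.139 to 0.135, and 0.130 to 0.133).

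**Cross-check by formula.** Let Rb and Rw be the assumed shares of between- and within-clinic variance explained. At ICC 0.05 the variance multiplier is 20 × 0.05 × (1 − Rb) + 0.95 × (1 − Rw).

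- Rb 10%, Rw 5%: multiplier 1.80, power 56.9%.
- Rb 25%, Rw 10%: multiplier 1.605, power 61.9%.
- Rb 50%, Rw 20%: multiplier 1.26, power 72.4%.

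This borrows a linear-model variance argument, so it is only a guide. Even its most favourable case stays below 80%.

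**The case against.** The strongest reply is that nothing here is invalid. A randomised comparison with a clinic random intercept and three covariates is sound, and a fourth covariate is a matter of efficiency. The article is condensed, its list is not worded as exclusive, and the trial design awaits the pilot results. The validity point stands in full. The rest stands in part: the article does name its covariates, so this concerns a stated choice, but the change could equally be made in the SAP, which is not shown.

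A reader might infer that, with 15 clinics per arm, chance imbalance in prior interruption biases the treatment effect. It does not. In the simulation the between-arm difference in prevalence had an SD of about 5 to 6 percentage points, but that is random error, carried in the standard error, and it does not inflate type I error.

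A reader might also expect larger gains from a variance cut of 1 − ρ²; with ρ = 0.5 it would lift 54% to 66%. The documents give no ρ, and the formula is a linear-model result applied equally between and within clinics.

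Nor do the documents show that most participants have a long dosing record. They give no distribution of time in treatment at enrolment, and the chart covers only the one clinic.

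The practical objections also have force. Missed doses sit in case notes, the wording and recall window of the survey items are not given, and patients are recruited after their clinic enrols, so assessment 1 may follow allocation. These limits shape the fix but do not remove the point.

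**Conclusion.** The point holds as a matter of efficiency. The primary model leaves out the baseline form of its own outcome, which the trial already collects, and so forgoes power if that history is prognostic. At 66% versus 55%, 600 patients and an ICC of 0.05, the likely gain on about 54% power runs from almost nothing (covariate HR 1.5) through 4 to 5 points (HR 2) to 8 to 10 points (HR 3).

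Those strengths are assumptions; the documents supply none. The simulation also used robust standard errors rather than the planned frailty model. The shortfall from 80% under clustering is a separate matter that this change would not repair.

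**What to change.** In the Statistical Analysis section, extend the patient covariates to *age, sex, time in MMT and baseline treatment interruption*, and settle this before the trial starts.

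- Use one prespecified definition, taken from the chart over a fixed look-back. End the look-back at the earlier of patient enrolment and clinic study launch, so that allocation cannot affect it.
- Add an indicator for patients without the full look-back.
- Do not mix the assessment 1 survey items into this covariate. Use them only in a sensitivity analysis.
- Report the model without the added covariate as a further sensitivity analysis.

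The cost is extra abstraction of the pre-enrolment chart period, from records the trial must already obtain for its primary outcome, and a hazard ratio conditional on one more covariate. No additional patients or visits are needed. The completed pilot may show how prognostic the covariate is.
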